### Sampling method

The sampling procedure is started by selecting provinces and districts in cooperation with the Ministry of Health. Next, among sub-districts with a moderate prevalence of wasting children, three are selected to become arms of the study. The prevalence rate of moderate wasting is 10–15%, and the decision to include moderate wasting is to maintain the heterogeneity conditions of the selected sub-districts. Three selected sub-districts are then selected randomly to be assigned as arm 1 (control) and arms 2 and 3 (intervention 1 and 2, respectively). Subjects are generated from *posyandu*, from which only those with 2–5 eligible children were chosen. Thus, to fulfil the total number of 30 subjects, each sub-district involves 6–15 *posyandu*. Expansion to another sub-district will be done when there are fewer than 30 wasting children aged 6–17 months in each selected sub-district. The sampling method scheme is provided in Fig. 3.

**Fig. 3 Fig3:**
[figure not shown]
Sampling method

This study comprises three arms, which are explained as follows:Arm 1 No Intervention: Control group.

The first arm is performed as a control group and does not receive biscuits but undergoes the routine IYCF counselling programme by a nutritionist from the health centre.Arm 2 First intervention group. This arm receives biscuits with portions as recommended by the Ministry of Health and obtains IYCF counselling by the nutritionist.

Subjects aged 6–11 months and 12–13 months should consume eight and twelve supplementation biscuits per day, respectively, based on the recommendation from the Ministry of Health, accompanied by participation in the routine IYCF counselling programme by the nutritionist from the health centre.Arm 3 Second intervention group (experimental). This arm receives the adjusted number of biscuits based on nutritional gap analysis.

The subject should consume four biscuits per day, for both children aged 6–11 months and 12–23 months. IYCF counselling is delivered with a specific message based on the nutrition gap analysis.

Due to the nature of the intervention, neither participants nor the health staff can be blinded to allocation but must not disclose the allocation status of the participant at the follow-up assessments.

### Patient and public involvement

This study would not involve any patient because participants who need medical treatment and have a severe food insecurity status of the households will be excluded. The results of the study will not be entirely disseminated to the study participants; nevertheless, the results of the anthropometric assessment and its changes will be provided to the participants’ mothers as a part of nutrition education. The health cadres will be trained at the preparation stage and involved in the study as an accompanying *Puskesmas* nutrition educator.

### Outcome measures

Primary: Nutritional status of wasting children.

The measurement will be recorded through study completion, from baseline and at third, sixth, and ninth months. Anthropometry measurements will be based on the weight-for-length indicator (WHO Child Growth Standards).Secondary: PMT biscuit compliance.

The measurement will be recorded through study completion, at the first to third months after the start of treatment and then at the sixth and ninth months from the beginning of treatment.

### Portion size adjustment according to nutritional gap analysis

The nutrient gap is a gap between the nutrient requirement and optimized nutrient intake that is identified using linear programming (LP) analysis and Optifood software using data regarding children under 2 years of age from a nationally representative study in Indonesia. LP analysis will identify problem nutrient(s), nutrient-dense food groups, subgroups, and food, as well as the optimized complementary feeding recommendation (CFR) [4]. The percentage of RDA gaps is calculated as the nutrient requirement subtracted by the percentage of nutrient requirement from the best diet in the LP analysis. The gap is converted into the required number of biscuits to ensure all nutrients can be fulfilled by the intake of complementary food plus the biscuits [10].

LP analysis found that the portion size of the biscuit provision should be reduced to only four biscuits for both children aged 6–11 months and aged 12–23 months. However, this new adjustment should be accompanied by IYCF practices with an emphasis on local food optimization. IYCF counselling is provided monthly by a nutritionist at Primary Health Care (PHC/*Puskesmas*) accompanied by cadres.

### Counselling of optimized CFR

The counselling session is conducted once a month for the first 3 months. Each education session takes 30–60 min prior to the distribution of food supplementation. Training to involve *Puskesmas*’s nutritionists and health cadres in the study area is conducted at the preparation stage to comprehend the nutrition counselling material for each arm. Every participant receives printed nutrition-promoting materials related to appropriate messages for each arm. The monthly meeting is also gathered to update field conditions during counselling.

The optimized CFR material and IYCF final version are sent by SEAMEO RECFON to each centre to be printed. The IYCF materials are prepared by the Ministry of Health, WHO and MCAI [11] with modifications of counselling materials initially targeting for 0–24 months of age.

### Assessing food insecurity in households

The assessment of food insecurity in households is conducted as a preliminary assessment to screen the subjects using structured interviews of the United States Household Food Security Survey Module (US-HFSSM) questionnaire, which focuses on assessing the ability of households to meet basic food needs and the subject’s habits and responses to the condition. There are 18 tiered questions to be given to the subject. These questions are also used to ensure that the poor nutritional status involved does not come from the severe food-insecure household. The categories of household food insecurity are based on the score of 0–2 as food secure, 3–7 as low food security, and 8–18 as very low food security.

### Anthropometry assessment

This study collects data on the weight and height of children to identify the nutritional status and characteristics of the children. This assessment was also used at the screening stage to select children according to the criteria. Wasting is defined as weight for a Z-score length less than − 2.00 [12].

Anthropometric training is conducted prior to data collection to ensure adequate precision and measurement accuracy—i.e., technical error of measurement (TEM) ≤0.7 cm and bias ≤0.7 cm compared with the results of criterion anthropometric measurements [13]. One researcher from each centre receives anthropometric training to standardize the measurement. Next, at each centre, the researcher trains all the data collectors and research assistants to perform the weight and length measurements (the calibration and placement of appropriate tools, the correct position of the subjects for measurement, correct reading, instructions to the subjects being measured, and recording the measurement results) [14].

#### Measurement of body weight

Body weight is measured in kilograms using SECA weight scales. The study maintains tools and measurements to ensure internal validity using the following considerations: the storage of tools must be kept in the horizontal position and shall always be put at the top of the pack, or at least, the items on it shall not exceed one kg.

Calibration of the instrument is performed daily to ensure that the tools work properly. The calibration uses a 1-kg calibration weight or 2 one-litre water mineral bottles as a substitute for the calibration weight. The weight of two mineral water bottles should not exceed a 0.01 kg difference between each measurement. The weighing is performed two times and always recorded in a special calibration note.

During the measurement process, the device should be used on a flat surface to maintain the stability of the measurement. Prior to weight measurement, the child should remove accessories that can affect the weight as well as height, such as shoes, socks, t-shirts, slings, hair pouches, hats or hoods. Diapers should also be removed before weighing and can be re-applied after weighing is complete. The research assistant explains to the mother/caregiver the process of weighing in advance.

Body weight is measured to the nearest 0.1 kg. The weight measurement is performed twice by a trained anthropometry team. When the difference between the first and second measurement is more than 0.2 kg, a 3rd measurement is performed. Two closest values are taken as the measurement result. Guidelines to determine the nutritional status of children are used from a decree that was released by the Ministry of Health of Indonesia in 2010 [14].

#### Measurement of body length

Height in children under 2 years is known as body length because the measurement is performed in the supine position. The instrument used to measure the length of the child is the Shortboard, with a precision of 0.1 cm. The length measurement requires at least two assistants and the mother/nanny. One person keeps the head touching the headboard and eyes at the Frankfurt plane position, the mother/caregiver in the middle is asked to hold the chest and lower thighs to keep the body straight, and one person is at the base, holding the mobile board to perform the measurement.

A flat area, slightly spacious and with sufficient lighting are required for length measurement. Like weight measurement, clothing or accessories that may affect the measurement results should be removed such as socks, shoes, hair pouches, hats or hoods. This process should be performed quickly because the child usually feels uncomfortable and wriggling makes it difficult to measure. The measurement is performed twice and so is the recording.

### Dietary assessment

Measurement of intake is performed using the (1) one-week-FFQ (Food Frequency Questionnaire), to measure the intake of nutrient-dense foods identified in optimized CFR, and (2) 24-h recall for 3 non-consecutive days (2 weekdays, 1 weekend), to measure the usual intake of macro and micronutrients in the population and measure the proportion of subjects at risk for inadequate iron intake and other micronutrients. The 24-h dietary recall interview is performed using a multiple-pass 24-h dietary recall [15]. The data are gathered from caregivers/mothers by mentioning all types of food consumed on the previous day. To obtain the same perception of food size, a standard “Food Photos Book” is used.

### Assessment of the perception of packaging and mode of delivery of supplemental biscuits

This question assesses the mother’s perception towards the supplemental biscuits to their children for the last 1 month. Assessment is performed using a Likert scale (best score = 5; 1 = least good score). The questions posed are the taste of PMT biscuits, suitability of the biscuit packaging in the form of biscuits given to the child according to the age of mother, suitability of the biscuit packaging (wrap and colour) regarding whether it is interesting and explanation to the mother how to feed the biscuits.

### Compliance to feeding instructions

Compliance assessment is performed by filling the record form given to the caregiver by the enumerators. Caregivers receive a monthly record form and are asked to complete the record every day. They should write down a reason when the biscuit eaten is less than the recommendation (only for 2nd and 3rd arm). The compliance form is collected monthly by the field team. The categories of compliance are grouped as follows: (1) Good, > 90%, (2) Medium, 80–90%; (3) Low, 60–80% and (4) Noncompliant, < 60%.

### Assessment of knowledge and practice based on IYCF

The infant and child feeding practices of caregivers are measured based on IYCF key indicators recommended by WHO/UNICEF and include dietary diversity, minimum meal frequency, and minimum acceptable diet, while the assessment of knowledge is generated from the practice indicators. There are ten questions of knowledge in the form of true-false questions.

### Place and time of execution

Data collection will be conducted in 7 selected sites in Indonesia in accordance with Ministry of Health Coordination (Sambas Regency - West Borneo [1.3625° N, 109.2832° E], Depok Municipality – West Java [6°24′8.94″S, 106°47′39.27″E], Padang Pariaman Regency – West Sumatra[0.5547° S, 100.2152° E], Sleman Regency – Yogyakarta [7.7325° S, 110.4024° E], Banjar Baru Municipality – South Borneo [3°27′26.07″S, 114°48′37.14″E], Sidoarjo Regency – East Java [7.4726° S, 112.6675° E], Makassar Municipality – South Sulawesi [5°8′39.76″S, 119°25′35.9″E]). Data from each site are collected by investigators from 7 research centres of respected universities in Indonesia (SEAMEO RECFON, Faculty of Public Health Universitas Indonesia; Faculty of Public Health Andalas University; Faculty of Public Health Lambung Mangkurat University; Faculty of Medicine, Public Health, and Nursing Universitas Gadjah Mada; Faculty of Public Health Airlangga University; Faculty of Public Health Hasanuddin University). SEAMEO RECFON serves as a lead investigator. This study is planned for 3 months using a grant scheme in 2017 so that implementation in the 6th and 9th months will be continued in 2018. The enrolment of the study participants was initiated in January 2018 and finalized in April 2018. It is expected that the final data collection would be in December 2018.

### Plan of data analysis and presentation

All data analysis will be performed using SPSS version 20. The data of the study subjects, both children characteristics and mother/caregiver characteristics, will be analysed to obtain the distribution frequencies and central tendencies as appropriate to the data scale. All subject characteristics of each arm will be analysed and compared with each other to assess their comparability at the beginning. No missing data are expected, and all loss to follow-up study participants will be excluded. The comparison of the weight-per-length score between groups and between times will be performed using ANOVA. The study subjects’ compliance to take biscuits will also be analysed and reported. The final dataset will be accessible to all authors without masking.

The research team is responsible to make annual and final reports to the Ministry of Health. The dissemination of the study results will be presented at the national nutritional meetings in the three regions. The scientific publications are the rights and responsibility of the research team.

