**Method:**

The efficacy of a government food supplementation programme will be examined using a randomized control trial design. Parents with wasting children aged 6–17 months will be recruited to participate in the study. After obtaining informed consent and pre-intervention measures, participants will be assigned into three arms of intervention with PMT biscuits and/or nutrition education only. The two primary outcomes for this study are the nutritional status of wasting children and PMT biscuit compliance. Characteristics of all subjects in each arm will be analysed and compared with each other to assess their comparability at the beginning. The data will be collected at pre-intervention, at 3 months of intervention, post-intervention, and at the 6- to 9-month follow up.

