### Data to be collected

The following data are collected based on the study subjects: subject characteristics (age, sex, and history of disease) and anthropometry (body weight and body height) data. Other data collected from the subjects’ mother/caregiver include the subject characteristics (demographic, socioeconomic, house condition), food intake of the child [using 24-h food recall for 3 days and last 1 week food frequency questionnaire (FFQ)], and perceptions of the supplemental biscuits (packaging and delivery method). The same method is also used to collect data for compliance with feeding instructions, exposure to information (health information sources, health information ever obtained in Posyandu/health services post), and IYCF-related knowledge. The flowchart for data collection is shown in Fig. 2.

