### Sample size

The sample size is calculated using the two means comparison formula. Based on Afarwuah, the standard deviation is obtained at 0.95 [9]. The sample size calculation is performed using the 95% confidence level, 80% power, and an estimated difference in the weight-for-length Z-score and drop-out of 0.30 and 20%, respectively. Based on the formula and data used above for the minimal sample size, 540 subjects are required for this study. Considering the feasibility of subject and study implementation, 90 subjects per district are required: 30 subjects as a control group or arm 1, and 30 subjects each as intervention group 1 or 2 (arm 2 or 3). Thus, a minimum of 6 districts is needed to meet the minimum sample size required.

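### Comparing all child and caregiver characteristics between arms, if done by child-level significance tests, cannot establish comparability; describe the baseline and fix covariates in advance (minor)

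*Protocol article*

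**What the plan says.** The section on data analysis and presentation of the protocol article has two steps for baseline data. The first is descriptive. It covers children and caregivers: "both children characteristics and mother/caregiver characteristics, will be analysed to obtain the distribution frequencies and central tendencies". The second is a comparison with a stated purpose: "All subject characteristics of each arm will be analysed and compared with each other to assess their comparability at the beginning". The Method paragraph of the abstract repeats it: "Characteristics of all subjects in each arm will be analysed and compared with each other to assess their comparability at the beginning".

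The section on data to be collected shows what would be compared. For the child it lists "subject characteristics (age, sex, and history of disease) and anthropometry (body weight and body height) data". From the mother or caregiver it lists "the subject characteristics (demographic, socioeconomic, house condition", without giving the number of items.

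The section on the sampling method fixes the unit of allocation: "Three selected sub-districts are then selected randomly to be assigned as arm 1 (control) and arms 2 and 3". Each district thus supplies one sub-district to each arm, with expansion to a further sub-district allowed where too few eligible children are found. The sample size section sets 30 children per arm in each district and at least 6 districts; the section on place and time lists 7 sites.

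ANOVA is named only for weight-for-length between groups and times. No covariate is named for it, and nothing is said to follow from the verdict on comparability.

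**The concern.** The descriptive step already covers frequencies and averages. The second step is separate and is meant to reach a verdict, so a reader may well carry it out with p-values. That would be the wrong tool, for two reasons.

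First, a baseline test asks whether a difference could be due to chance. It does not ask whether the difference is large enough, in a characteristic related to weight-for-length, to distort the outcome comparison. An influential imbalance can be non-significant, and a trivial one can be significant.

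Second, a test on children treats about 180 children per arm as independent when about 6 or 7 sub-districts per arm were allocated. Socioeconomic and housing data are recorded for each household, but may well be alike within a sub-district. The test would then call ordinary chance differences significant too often.

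Two things are at stake: a report that calls the arms comparable or not on poor evidence, and covariates chosen from the baseline table.

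**Working it through.** **What the plan gives.** It states no error rate for the baseline comparison, so there is no figure of its own to reproduce. The only significance level is in the sample size section ("The sample size calculation is performed using the 95% confidence level, 80% power"), and it concerns the outcome. Applying 5% to each baseline test is an assumption made here.

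**Layout.** 3 arms × 6 districts × 30 children = 540, which is 180 per arm and agrees with the stated total.

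**Assumptions.** One continuous characteristic with total variance 1 and no true difference between arms; one-way ANOVA on children that ignores sub-district and district. Let ρ be the ICC, the share of variance due to all clustering, and s the part of that share lying between districts. The documents give neither, so both are shown as ranges.

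**Formula.** Every arm contains every district once, so district effects cancel between arms. The variance of an arm mean, relative to the value the test expects, is then about

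g = 30(1 − s)ρ + (1 − ρ).

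The critical value of F with 2 and 540 − 3 = 537 degrees of freedom is 3.01. With 2 numerator degrees of freedom, the rejection rate is approximately exp(−3.01/g).

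**All clustering between sub-districts within district (s = 0, so g = 1 + 29ρ):**

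| ρ | g | Formula | Simulated |
|---|---|---|---|
| 0 | 1.00 | 5% | 5% |
| 0.02 | 1.58 | 15% | 15% |
| 0.05 | 2.45 | 29% | 28–31% |
| 0.10 | 3.90 | 46% | 47% |
| 0.20 | 6.80 | 64% | 65–66% |

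The simulated column comes from several runs of 4,000 to 6,000 null baselines. Seven districts give nearly the same rates.

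**Clustering partly between districts, ρ = 0.05:**

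| s | g | Formula | Simulated |
|---|---|---|---|
| 0 | 0.75 × 2 + 0.95 = 2.45 | 29% | 28–31% |
| 0.5 | 0.75 + 0.95 = 1.70 | 17% | 17–18% |
| 0.8 | 0.30 + 0.95 = 1.25 | 9% | 9% |
| 1 | 0 + 0.95 = 0.95 | 4% | 4% |

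The inflation therefore depends on how much of the clustering is local to the sub-district. With clustering wholly between districts there is none, and the rate is slightly below 5%.

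**Several tests.** For k independent tests at rate p, the chance of at least one flag is 1 − (1 − p)^k. At p = 0.05 this is 1 − 0.95^5 = 23% for the five listed child items and 1 − 0.95^8 = 34% if the three caregiver domains count as one item each. These figures need no clustering, but they assume independence.

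**The case against.** The strongest reply is that the plan does not announce any test. It says the characteristics will be compared, and comparing frequencies and averages by arm is an ordinary baseline table with no false-positive rate. That stands. The over-flagging is conditional on a choice that the text permits but does not make.

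A second reply is that a look at comparability is useful here. Few units are allocated, children are recruited within them, and the trial is open-label, so real imbalance is possible. That also stands. It supports describing the baseline, by sub-district as well as by arm; it does not make a p-value evidence of balance.

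A third reply is that districts act as blocks. The sites lie in seven different provinces, so much of the similarity between households may be between districts and hence balanced. The second table shows that this can remove the inflation altogether, so the 30% figure should not be quoted without its condition.

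A reader might go further and infer that the plan will almost certainly report false differences: with ten characteristics at p = 0.30, 1 − 0.70^10 = 97%. The documents do not support this. It needs ten independent characteristics, all with a within-district ICC of 0.05, all tested at child level. Age, weight and length are correlated, and no ICC is given for any item.

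A reader might also infer that the verdict would decide whether the outcome analysis is adjusted. The plan contains no such rule.

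**Conclusion.** The point holds in a limited form and is minor. The protocol article plans to judge comparability by comparing all child and caregiver characteristics between arms, and leaves open how. If child-level significance tests are used, they cannot establish comparability. They would flag chance differences in about 15% of tests at a within-district ICC of 0.02 and about 30% at 0.05, and in about 5% or slightly fewer if the clustering lies between districts. These rates rest on an assumed 5% level, assumed ICCs, about 6 to 7 sub-districts of 30 children per arm, and an analysis that ignores clustering.

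No outcome result depends on the verdict as the plan is written. The direct effect is a possibly misleading statement about baseline balance. The indirect one is a risk that covariates are chosen after the table is seen, because the outcome ANOVA names none. How that ANOVA handles clustering is a separate question, which this point does not settle.

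**What to change.** Replace the sentence in the data analysis section, and its counterpart in the abstract, with wording such as:

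*Baseline characteristics of children and caregivers will be summarised by arm and by sub-district. Imbalance will be described by its size (standardised difference), without significance tests. Baseline weight-for-length z-score, child age, sex, household food-security score and district will be included in the weight-for-length model whatever the baseline table shows.*

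All of these are already collected at screening or baseline, and district is the block within which sub-districts are allocated. If baseline z-score is a covariate, the modelled outcomes should be the values at months 3, 6 and 9, so that the baseline value is not on both sides of the model.

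The cost is small. The baseline p-value column is lost and one column of standardised differences is added. With 6 districts the covariates use 4 + 5 = 9 degrees of freedom, taking each of the four others as a single term; with 7 districts they use 10. The gain is an adjustment that cannot be steered by the baseline table, and probably some precision. The documents give no correlations from which that precision could be calculated.

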### Study subjects

This study uses the following inclusion criteria: children aged 6–17 months with a weight-for-length z score less than 2.00 to − 2.99 considering that the children are still categorized as children under 2 years of age at the end of the intervention. The other criterion is that they do not receive the biscuits at the time of recruitment and the subjects’ parents agree to participate in the research by signing the informed consent document.

During the determination of study eligibility, four populations were identified that are inappropriate for entry into the food supplementation (biscuit) randomized controlled trial, including the severe wasting (weight-for-length less than − 3 Z-score) population because it needs to be treated differently and because it is strongly associated with a very high short-term mortality risk [7].

The exclusion criterion of this study is a severe food insecurity status of the households because their access to nutritional food is severely hampered, affecting not only the young children but also all family members.

Despite poor dietary intake, infection is also considered a determinant of nutritional status; therefore, having tuberculosis infection (based on anamnesis) is also used to exclude the subjects. Having TB infection as a co-infection in parallel with acute malnutrition was found to be a predictor of child mortality [8].

To minimize the loss to follow-up subjects, the possibility of moving to other cities within 6 months of intervention is also listed as an exclusion criterion. All the terms and conditions of the study will be explained before the caregiver/parents sign the inform consent documents.

Adverse events will be recorded and immediately reported to the PIC through the centres’ coordinators, and those affected will be referred to the nearest public health centres involved in the study. All severe adverse events will be reported to the Health Research Ethics Committee of FKUI/RSCM.

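### The protocol excludes every child lost to follow-up although it allows for 20% drop-out, so the primary comparison rests on completers only

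*Protocol article*

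**What the plan says.** The section Plan of data analysis and presentation gives the rule in one sentence: "No missing data are expected, and all loss to follow-up study participants will be excluded". It then names ANOVA for comparing WLZ between groups and between times.

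Three other sections bear on this:

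- Sample size assumes "an estimated difference in the weight-for-length Z-score and drop-out of 0.30 and 20%, respectively".
- Study subjects tries to limit loss by excluding children at entry for "the possibility of moving to other cities within 6 months of intervention".
- Outcome measures schedules the primary outcome "from baseline and at third, sixth, and ninth months".

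The Methods/design section describes an open-label trial with three months of intervention in arms 2 and 3. Arm 1 receives no biscuits. The Sampling method section assigns arms by sub-district.

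**The concern.** The protocol fixes this rule itself, so an analysis plan that followed it would inherit the problem. Three things follow from it.

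1. The expectation of complete data sits badly with a 20% drop-out allowance and with an entry criterion meant to limit loss.
2. The sentence excludes participants, not visits. A child measured at months 3 and 6 and lost before month 9 would also leave the month-3 comparison, which is the end of treatment.
3. The analysed set is defined by something that happens after assignment. Families know their arm, and one arm gets no product, so reasons for staying may differ between arms. If they do, the completers are no longer comparable groups.

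At stake are precision at the visits where most children were seen, and the validity of the primary comparison.

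**Working it through.** **Inputs from the Sample size section.** "The sample size is calculated using the two means comparison formula". SD: "the standard deviation is obtained at 0.95". "The sample size calculation is performed using the 95% confidence level, 80% power". Difference 0.30, drop-out 20%, total 540, equal arms, so 540 / 3 = 180 per arm. A two-sided test is assumed, because sidedness is not stated. Clustering by sub-district is ignored throughout, so the power figures are optimistic.

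**The plan's own figure.** n per arm = 2 × (1.96 + 0.8416)² × 0.95² / 0.30² = 157.4, rounded up to 158. Allowing for drop-out:

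- 158 / 0.80 = 197.5, so 198 per arm and 594 in total.
- 158 × 1.20 = 189.6, so 190 per arm and 570 in total.
- One-sided: 124 per arm before loss, giving 465 or 447 in total.

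None of these gives 540. With 180 per arm, the loss that still leaves 158 is 1 − 158/180 = 12%. Why 540 does not reproduce is a separate matter. It matters here only because 540 leaves little room for exclusions.

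**Children removed at the planned loss.** 0.20 × 540 = 108, or 36 per arm, leaving 144 per arm. The 108 is an upper bound on children whose post-baseline values would be discarded, since those lost before month 3 have none.

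**Power for a 0.30 difference.** Power = Φ(0.30 / (0.95 × √(2/n)) − 1.96).

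| n per arm | Situation | Standard error | Power |
|---|---|---|---|
| 180 | 540 enrolled, all analysed | 0.1001 | 85.0% |
| 144 | 540 enrolled, 20% excluded | 0.1120 | 76.4% |
| 168 | 7 sites × 90 = 630 (assumption), 20% excluded | 0.1037 | 82.5% |

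**Bias.** Suppose lost children are g lower in WLZ than retained children of the same arm, with the same g in both arms. The completers' mean in an arm then exceeds the full-arm mean by g × (loss in that arm). Hence

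bias in (biscuit − control) = g × (loss in biscuit − loss in control).

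- Equal loss: g × 0 = 0.
- Assumed loss of 10% in a biscuit arm and 30% in control, g = 0.3 to 0.5: 0.3 × (−0.20) = −0.06, and 0.5 × (−0.20) = −0.10 z. That is 20% to 33% of the 0.30 target, and it works against the biscuits.

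The losses and g in the second case are assumptions; the protocol gives none of them by arm.

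**Simulation check.** Assumed: 180 per arm, SD 0.95, autoregressive correlation 0.7, true difference 0.30, about 20% lost after month 3 depending on month-3 WLZ. With the same mechanism in both arms, completers-only gives 0.30. With opposite mechanisms (poor growers leave control, good growers leave the biscuit arm), completers-only gives −0.06 at month 3 and 0.12 at month 9. Using the observed values of the lost children as well gives 0.30 and 0.29. This second case is deliberately extreme. It shows that equal loss rates alone do not protect the comparison.

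**The case against.** The strongest reply is that the two statements can be reconciled. Inflating a sample for drop-out is what one does when lost children will not be analysed, and the expectation of complete data may concern only gaps among retained children. That reading is fair, so a flat contradiction should not be claimed. It leaves the exclusion rule untouched: inflation protects power, not comparability.

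Other points stand in whole or in part:

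- The text does not say whether exclusion applies to all visits or only to the missed ones. Participant level is the natural reading, but it is not explicit. If exclusion were per visit, month-3 values would survive and the month-9 comparison would still be completers-only.
- A reader might count 126 children with discarded visits (0.20 × 630). The document states 540. The 630 assumes 90 children at each of the seven listed sites, and not every lost child has a post-baseline visit to discard.
- A reader might infer that sicker children leave for treatment. Nothing in the protocol supports this.
- The power loss depends on enrolment. At 630, 168 per arm remain, more than the 158 that the inputs require.
- The six-month limit in the moving criterion, shorter than the nine-month follow-up, is a measure to reduce loss and not an error.
- Detailed sensitivity analyses are commonly left to an analysis plan. Their absence is not the point; the stated exclusion is.

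**Conclusion.** The concern holds as a defect in a stated rule. Followed as written, the primary WLZ comparison uses a set of children selected after assignment and, on the natural reading, discards valid earlier visits.

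For precision, up to 108 of 540 children are removed and power is about 76% instead of 85%. If 630 are enrolled, power after loss is about 82%. These figures rest on a two-sided 5% test, the plan's SD and difference, 20% loss in every arm, and no clustering.

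For validity, a reader might infer that the rule breaks the randomised comparison or that the result will be biased. The documents do not support that. Bias needs loss, or the mechanism behind it, to differ between arms, and the protocol gives no information on either. An open label and a control arm without biscuits make a difference plausible. The −0.06 to −0.10 z is an illustration of what could happen, not an estimate.

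**What to change.** Delete the sentence on missing data and exclusion, and replace it with a rule along these lines:

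- Analyse all children in the arm assigned to their sub-district, using every available visit.
- Fit a linear mixed model for WLZ with arm × visit and random effects for child and sub-district. Include baseline WLZ as an outcome; a model of months 3, 6 and 9 alone could not include children lost before month 3. These children add little information on the arm difference, but they stay in the analysed set. The model is valid if loss depends only on observed values.
- Report loss by arm.
- Add one sensitivity analysis for informative drop-out, in which lost children are assumed to do worse than the model predicts.

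The cost is a change of analysis wording and slightly more analysis work. No further children, visits or measurements are needed.
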